## 3. Intervention

### 3.1. Rationale

The intervention was based on the Mothers and Babies Course [53] for the prevention of postpartum depression. This intervention has demonstrated strong empirical evidence for preventing perinatal depression [19].

The Mothers and Babies Course is based on the principles of cognitive behavioral therapy (CBT) and attachment theory and includes three sections that address the main components of CBT: thoughts, pleasant activities, social contacts. Cognitive behavioral therapy is one of the most studied interventions for the treatment and prevention of postpartum depression. The Mothers and Babies Course uses a healthy management of reality model that helps women recognize how their internal and external realities can affect their mood, and how to manage their thoughts, behaviors, and relationships to promote healthy emotional states and reduce the risk for depression [3]. Elements of attachment therapy are also integrated into the app with guidelines for developing a secure attachment with their baby and promoting the connection between the mother and the positive impact it has on her child. In addition, the Healthy Moms and Babies application includes content on problem solving and decision-making, relaxation training, and demystifying misconceptions and biases about motherhood.

Cognitive behavioral therapy appears to be the most empirically supported therapeutic approach [54,55]. Evidence indicates that CBT interventions are efficient and cost-effective in treating and preventing perinatal depression [54,56], and reducing symptoms and the progression of postpartum depression [55].

A multidisciplinary team of psychologists and obstetricians developed the content of the app by discussing and reflecting on the important topics to be included. First, the existing literature on preventive interventions for postpartum depression was reviewed, and the intervention’s content and activities were analyzed. Then, e-health interventions were examined to delve into their structure, function and other interesting elements in the online intervention. Based on the framework of the Mothers and Babies Course [53] and other literature reviews, one part of the team of professionals drafted the content script, and the other part performed a subsequent check, which included making appropriate modifications.

### 3.2. Goals of the Intervention

The primary objective of the e-health intervention application Healthy Moms and Babies was the prevention of depressive symptomatology during the postpartum period. The secondary objective was to prevent anxious symptoms after childbirth. Additionally, the application aims to raise awareness among pregnant women about the importance of taking care of their mental health and psychological well-being and the positive effects of taking care of their own well-being on their baby’s well-being.

### 3.3. Overview of the Intervention

The psychological intervention was comprised of eleven modules with a similar structure: an introductory video, psychoeducational content, a practical exercise, general guidelines, and motivational messages. Considering that a new module was released every 4 days, the average duration of the intervention was six weeks. The components of the intervention are described in the following paragraphs and Table 1.

*Module 1. You are a mum:* welcomes, collects and validates all the emotions and sensations that a pregnant woman may experience, inviting her to make use of the app to live consciously during her pregnancy. The practical activity allows the participant to reflect on her emotions related to her pregnancy.

*Module 2. Psychoeducation:* validates any emotions related to pregnancy and motherhood, reducing guilt, and encouraging responsible action. It provides some facts and information about the baby blues, perinatal depression, and its consequences. The practical activity consists of pointing out the depressive symptoms with which the woman identifies and naming the situations in which she does so.

*Module 3. Feel better:* presents the story of Violeta and María, two women who encounter the same day, but with very different experiences. It addresses the individual responsibility of making choices to increase the feeling of well-being. The practical activity invites the participant to create positive loops of activities, thoughts, and emotions to help her through difficult moments.

*Module 4.**Thoughts:* proposes that the participant listens to her thoughts and identifies the emotions she feels with each thought, inviting her to question them, release them or reformulate them when they generate discomfort and do not conform to reality. In the practical portion, the app challenges the woman to transform her most negative and harmful thoughts into healthier ones.

*Module 5.**Enjoy the day:* addresses the importance of planning and prioritizing pleasant activities each day, highlighting their potential benefits for emotional health. It proposes that the participant reflects on five pleasant activities that can be done in their daily life and offers guidelines for time management and how to practice these guidelines daily.

*Module 6.* Relax: relaxation is presented as a deactivation technique in stressful situations. The app offers women five relaxation audio clips and invites the women to practice them during pregnancy and after childbirth with their baby.

*Module 7.**Your body:* this module is the only one that does not propose a practical or reflective activity, and its content is basically informational. It provides information on the most common bodily and physiological changes during pregnancy.

*Module 8.**Find a solution*: differentiate between proactive and reactive tasks or emotion-focused coping strategies. The app proposes that the participant reflects on the aspects of her life that she wants to improve and invites her to look for alternative coping techniques to those she has used thus far.

*Module 9.**Social support*: highlights the importance of social support and differentiates between the different types. It also offers guidelines for assertive communication in the active search for support. This module suggests that the participant writes down a list of people who can provide support and suggests that she reflects on her support needs during pregnancy and the postpartum period.

*Module 10.**Goodbye myths*: uncovers the preconceived misconceptions about motherhood that can lead to frustration and suffering.

*Module 11.**Your baby*: addresses the participant’s expectations of what her baby will be like. It also offers some general guidelines for developing a secure attachment bond and some specific tips for handling very demanding babies.

### 3.4. Email Reminders to Increase App Utilization

When the app detects that the participant has not progressed in the modules for several days or weeks, it will send an email reminder to the mother to: (a) encourage continuing participation with the app, (b) inform the participant of subsequent topics; (c) offer the opportunity for the participant to ask questions or request support in the use of the tool; and (d) provide instructions to activate notifications as to when the next psychological module will be unlocked. If the participant continues to not use the application, up to three emails will be sent encouraging her to do so; following this, the participant is considered lost to follow-up.

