### 2.3. Outcomes and the Allocation of Participants to Trial Groups

#### 2.3.1. Primary Outcome

The primary outcome measure will be the difference in the mean scores between the intervention and control groups on the Patient Health Questionnaire-9 (PHQ-9) at the end of the psychological modules of the Healthy Moms and Babies application (in the case of the control group, the post assessment will be done six weeks after starting the PPP for the first time) and at three and six months after the delivery date.

The PHQ-9 is a nine-item instrument that assesses the severity of depressive symptomatology according to the following criteria of the Diagnostic and Statistical Manual of Mental Disorders [47]: depressed mood, markedly diminished interest in usual activities, significant increase or loss of appetite/weight, insomnia/hypersomnia, psychomotor agitation/retardation, fatigue or loss of energy, feelings of worthlessness or guilt, difficulty with thinking, concentrating or making decisions, and recurrent thoughts of death or suicide. The items are rated on four-point Likert-type scales, ranging from 0 (never) to 3 (almost every day), with higher scores indicating high severity of depressive symptoms (range 0–27). A score of 10 is the cut-off point recommended in clinical practice for estimating the presence of depressive symptoms [48,49]. However, considering that our aim is to prevent depressive symptoms, we will include all pregnant women who obtain a score equal to or greater than 5. The PHQ-9 has been validated in Spanish-speaking samples and in Spanish pregnant women [50].

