### 2.5. Randomization

When participants access the Healthy Moms and Babies application for the first time, they will complete the baseline assessment including the PHQ-9 and GAD-7. Only participants who score between 5 and 19 on the PHQ-9 will be included and randomized into the treatment and control groups.

Based on the PHQ-9 score, called the $value, the Plesk software will distribute participants according to their level of symptomatology. Participants scoring <5 on the PHQ-9 have minimal depressive symptoms and therefore they will be excluded from the study and no further evaluation will be performed, but they will be offered access to the pregnancy information content. Participants scoring >19 on the PHQ-9 are considered to have severe symptomatology and will also be excluded from the study. In this case, these participants will be blocked from accessing the Healthy Moms and Babies application because it was not designed to address severe depressive symptomatology. Women will receive an alert message telling them to share their distress with someone close to them and to see a specialist for appropriate psychological care. Eligible patients (PHQ-9 score between 5 and 19) will be randomly assigned to the intervention and control groups according to the standard PHP function (mt_rand()) automatically generated by a computer. Women in the intervention group will have access to the psychological content modules and the general pregnancy information on the Healthy Moms and Babies app; women in the control group will only be able to access the informational content.

An independent researcher will program the mathematical algorithm that performs the randomization. Subsequently, simple blinding will be used, and participants will not be informed of the group to which they are assigned. The allocation will be known to the study team after it is performed automatically.

Outcome measures will be assessed at baseline, immediately after the intervention, and three and six months after the delivery date. At follow-up, questionnaires will be sent at the appropriate time by email and will be completed by the women via a web form.

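### Section 3.4 classes women who stop using the app as lost to follow-up, although their 3- and 6-month outcomes need no app use; the trigger fits only the intervention arm, so the primary comparison could be biased in either direction

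*Protocol article*

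**What the plan says.** **The rule (protocol article, section 3.4).** The reminder sequence starts "When the app detects that the participant has not progressed in the modules for several days or weeks". One purpose of the reminder is to "provide instructions to activate notifications as to when the next psychological module will be unlocked". If the woman still does not use the app, "up to three emails will be sent encouraging her to do so; following this, the participant is considered lost to follow-up".

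**Who has modules (section 2.5).** "Women in the intervention group will have access to the psychological content modules and the general pregnancy information", whereas "women in the control group will only be able to access the informational content".

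**How follow-up outcomes are collected (section 2.5).** "At follow-up, questionnaires will be sent at the appropriate time by email and will be completed by the women via a web form".

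**When the post assessment takes place (section 2.3.1).** For women given the modules it falls "at the end of the psychological modules of the Healthy Moms and Babies application". Controls are instead put on a fixed clock that does not depend on use: "in the case of the control group, the post assessment will be done six weeks after starting the PPP for the first time".

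The PHQ-9 at the post assessment and at 3 and 6 months after delivery forms the primary outcome, and section 2.9 compares its mean between the two arms. The Discussion (section 4) warns that online interventions can have high drop-out and low adherence, but gives no rate.

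**The concern.** Stopping the intervention and failing to supply an outcome are different events. Section 3.4 defines the second by the first: the test is use of the app, not an unreturned questionnaire. For the 3- and 6-month time points this loss is avoidable, because the woman has an email address on file and the form lies outside the app.

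The rule also appears to act on one arm. Progress in the modules can stall only where there are modules, and no inactivity rule is given for controls. If it is applied as worded, the intervention mean would rest on women who kept using the app, while the control mean would rest on all controls who reply. Randomisation does not protect that comparison. Any link between disengagement and mood would enter the estimated effect. No analysis plan written later can recover questionnaires that were never sent.

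**Working it through.** **1. Reading the sections together**

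| Question | Intervention arm | Control arm |
|---|---|---|
| Psychological modules? (2.5) | Yes | No |
| Can module progress stall? (3.4) | Yes | No modules to stall |
| Inactivity rule ending in loss to follow-up? (3.4) | Yes, after up to three emails | None stated |
| 3- and 6-month outcome needs the app? (2.5) | No, emailed web form | No, emailed web form |
| Timing of post assessment (2.3.1) | End of the modules | Six weeks after first start |

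The last row points the same way. A woman who never finishes the modules has no defined post assessment, whereas a control has one regardless of use. How the post assessment is administered is not stated; the emailed form is stated only for follow-up.

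**2. The plan's own figure**

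Section 2.8 gives a minimum of 385 with alpha 0.05 and heterogeneity of 50%. This reproduces as the precision size for a single proportion, if a margin of 0.05 is assumed (the margin is not stated):

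n = 1.96² × 0.5 × 0.5 / 0.05² = 384.1, rounded up to 385.

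The point here does not depend on that figure. It only supplies arm sizes for the illustration: 192 and 193.

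**3. Illustration of the bias**

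Assumed inputs, none of them in the documents:
- no true effect, and every control retained;
- SD of PHQ-9: 4.5, with 5 as a check;
- q, the share of the intervention arm dropped by the rule: 0.2 to 0.5;
- D, the mean PHQ-9 of dropped women minus that of retained women: 0 to 3 points, either sign.

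Formulae:
- Spurious difference = q × D (full-arm mean minus the mean of retained women).
- SE = SD × √(1/(192(1 − q)) + 1/193).
- With z = q × D / SE, two-sided false-positive rate = Φ(−1.96 + z) + Φ(−1.96 − z).

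Worked cases, SD 4.5:
- q = 0.3, D = 2: difference 0.6; SE = 4.5 × √(1/134.4 + 1/193) = 0.506; z = 1.19; rate 22%.
- q = 0.4, D = 2: difference 0.8; SE = 4.5 × √(1/115.2 + 1/193) = 0.530; z = 1.51; rate 33%.

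False-positive rate, SD 4.5:

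| q | D = 0 | D = ±1 | D = ±2 | D = ±3 |
|---|---|---|---|---|
| 0.2 | 5% | 7% | 13% | 23% |
| 0.3 | 5% | 9% | 22% | 43% |
| 0.4 | 5% | 12% | 33% | 62% |
| 0.5 | 5% | 14% | 43% | 76% |

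With SD 5 the two worked cases give 19% and 27%.

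The sign of D sets the direction. If dropped women are worse (D > 0), the app looks better than it is. If they are better, the app looks worse, and a real benefit could be hidden. If D = 0, this rule adds no bias.

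**4. Precision**

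The difference detectable with 80% power is (1.96 + 0.84) × √(1/193 + 1/(192(1 − q))) SD. It is about 0.29 SD with full retention, 0.30 SD at q = 0.2 and 0.35 SD at q = 0.5. That loss is modest; the concern is bias.

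**The case against.** The best case against this point is that section 3.4 is about engagement. Its heading concerns reminders to use the app, and it says nothing of outcome collection or analysis sets. Section 2.5 states without exception that follow-up questionnaires will be emailed, and section 2.9 excludes nobody. On that reading the reminders simply end, and the label is loose wording.

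This stands in part. A reader might infer that the protocol withholds questionnaires from these women, or that the primary analysis is intervention adherers against all controls. The documents say neither outright. What they do is apply a label that ordinarily means no further outcome data, and they nowhere say that it means something else here. The two sections need to be reconciled.

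Four further limits hold:
- That only the intervention arm can trigger the rule is a strong inference, not a statement. The final step speaks of not using the application, which controls also have. But it continues from a trigger based on modules, and the reminder text concerns unlocking the next psychological module. If controls were covered too, non-adherence would still be recorded as loss.
- A reader might infer that every primary time point is collected outside the app. That is stated for 3 and 6 months only.
- A reader might infer that the bias must favour the app. Low mood may cause disengagement, but women who feel well may also stop. The documents do not settle the sign.
- The absence of a fully defined analysis population is not counted here, since an analysis plan that is not shown may contain it.

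**Conclusion.** The point holds as a conflict in the wording that can do real damage if section 3.4 is followed as written. It merges non-adherence with outcome loss, and does so mainly or only in the intervention arm, although the 3- and 6-month outcomes remain obtainable.

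Its size cannot be derived from the documents. With no true effect, SD 4.5, and 30% to 40% of the intervention arm dropped with PHQ-9 differing by 2 points from those retained, the spurious difference is 0.6 to 0.8 points and the false-positive rate about 22% to 33%, against a nominal 5%. These figures show what could happen, not what the trial will produce. They also assume full response among controls; ordinary non-response to the web form would affect both arms.

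The rule should be corrected, because the primary comparison is exposed and the correction is cheap.

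**What to change.** Replace the last clause of section 3.4 with wording to this effect:

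- After three reminder emails without renewed use, the participant is recorded as having discontinued the app. She is still sent the PHQ-9 and GAD-7 at 3 and 6 months and at the post assessment, and stays in her randomised group for the comparison.
- A participant is lost to follow-up for a given time point only when its outcome questionnaire has not been returned after reminders. The same questionnaire-reminder rule applies in both arms.

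Reconcile this with section 2.3.1, so that the post assessment of women who do not finish the modules has a defined time that does not depend on finishing them.

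Cost: a change of wording and a few more questionnaire emails and reminders. The estimated effect may come out smaller, because women who stopped using the app are counted in the arm to which they were randomised.

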### 3.5. Intervention Quality Control Procedures

The Healthy Moms and Babies application was developed by a research team comprised of professionals in the field of health psychology and obstetrics. Email contact with the participants will be carried out by a psychologist from the team who is trained to respond to any clinical/crisis needs that may arise.

### 3.6. Usual Care

The Moms and Babies application does not interfere with the usual care that the pregnant women receives and is not incompatible with any other type of psychological intervention. Women who score <5 on the PHQ will be excluded from the study, and will be offered access to the general content of the application and information on breastfeeding, nutrition, and physical activity.

## 4. Discussion

Perinatal depression can threaten the physical and psychological health of the mother, put the baby’s development at risk, and affect the creation of the bond between mother and baby, the couple’s relationship, and the family [16]. To avoid these negative consequences, health providers [34] and institutions [19] must stress the need to implement preventive interventions for perinatal depression. Pregnancy is a favorable time to address prevention [3,24]. However, help-seeking rates during this period are low due to multiple barriers and difficulties, including the lack of information, costs of access to conventional treatments, and fear of stigmatization and public exposure to peers [33,34].

E-health interventions, including mobile applications, offer advantages in overcoming the barriers described above, facilitating access to interventions at low costs and in a simple way. Moreover, these applications can reach women all over the world, including those women who experience difficulty traveling to receive health services [57,58]. Digital tools offer new and tailored content, allowing women to access the tools at their own pace and preserving their anonymity [59].

However, despite the many virtues of online interventions [60], they also have some limitations. Participation and retention can be difficult to sustain in an online intervention, leading to high drop-out rates and low adherence [29]. It is therefore, important to consider the additional moderation of the intervention by a professional, analyze women’s use of the tool, and adapt the application to their needs as much as possible [61].

Mental health applications are not intended to replace professional clinical services. Instead, these apps can be a cost-effective, easily accessible, low-intensity resource for women who are unable to receive standard psychological treatment, or a good complementary resource to face-to-face counseling. The Healthy Moms and Babies app was developed by a multidisciplinary team that aims to contribute to increasing the scientific evidence on the effectiveness of CBT-based mobile applications to prevent postpartum depression.

## 5. Conclusions

This study contributes to efforts to make depression prevention a priority [37]. From a public health perspective, there is a need to address maternal mental health and technology-based resources can serve as a tool to help pregnant women and new mothers cope with perinatal depression symptoms

## Figures and Tables

**Figure 1 ijerph-18-12485-f001:**
[figure not shown]
Flowchart of the study design.

**Table 1 ijerph-18-12485-t001:** The components of the intervention.

Welcome	Content Always Available	General Information
[figure not shown]	Info about the Healthy Moms and Babies app FAQs about pregnancy and childbirth Infant development Videos on childbirth Configuration of the app	Breastfeeding Feeding Physical activity
**Psychological Content**		
**Module 1**	**Module 2**	**Module 3**
**You are a mum**	**Psychoeducation**	**Feel better**
[figure not shown] Collects and validates your emotions. Invites you to use the app.	[figure not shown] Info on PPD and its symptoms.	[figure not shown] Well-being, enhancing decision-making.
**Module 4**	**Module 5**	**Module 6**
**Thoughts**	**Enjoy the day**	**Relax**
[figure not shown] Cognitive restructuring, adjusting to reality, defusion strategies.	 Behavioral activation with enjoyable activities. Time management and planning.	 Relaxation audio clips for deactivation in stressful situations.
**Module 7**	**Module 8**	**Module 9**
**Your body**	**Find a solution**	**Social support**
[figure not shown] Info on body and physiological changes in pregnancy.	[figure not shown] Coping and problem-solving strategies.	[figure not shown] Info on social support, assertive communication guidelines and support-seeking.
**Module 10**	**Module 11**	
**Goodbye myths**	**Your baby**	
[figure not shown] Myths about motherhood and their demystification.	 Addresses the woman’s expectations of the baby and guidelines for secure attachment development.	

